### Blinding

This study adopts a single-blind (patient-assessor–blinded) method. Except for the acupuncturists, other personnel, including all participants, outcome assessors, data analysts, and statisticians, will be blinded to the patients’ grouping. To reduce communication and contact between patients, we will assign patients to receive treatment in different rooms. During the entire treatment period, patients should wear eye patches. Blind evaluation will be used by the evaluator to assess and record various observation indicators. To ensure the safety of the study data, we will set up a data safety monitoring committee in accordance with the guidance of the Data Safety Monitoring Board (DSMB). The data will ultimately be summarized by third-party blind statistical analysis.

### Intervention

All study participants will be randomly assigned to either the electroacupuncture group or the sham electroacupuncture group in a 1:1 ratio, receiving treatment 3 times per week for 4 weeks. At the same time, we will keep records of actigraphy for patients at week 0, week 1, week 2, week 3, and week 4. Allocation of participants will be conducted by a licensed acupuncturist with more than 2 years of clinical experience. Except for the acupuncturists, the study investigators, participants, outcome assessors, study staff, and statisticians will all be blinded to the allocation. Before treatment, we will perform skin sterilization for patients. If patients experience severe physical discomfort due to insomnia, we will prescribe appropriate medication based on their conditions. During the medication period, we will strictly record the name, dosage, and administration method. Relevant investigators will also record the medication taken by patients on a CRF.

### Electroacupuncture Treatment (Electroacupuncture Group)

Patients in the electroacupuncture group will receive electroacupuncture performed by acupuncturists. Stainless steel 0.25×40 mm acupuncture needles (Suzhou Yan yi Medical Technology Co, Ltd) will be inserted into 6 acupoints, including Bai Hui (GV20), Shen Ting (GV24), Yin Tang (GV29), An Mian (EX-HN22), Shen Men (HT7), and Nei Guan (PC6) acupoints (Figure 1; for acupoint location, refer to The Location of Acupoints: State Standard of the People’s Republic of China [GB/T 12346‐2021] [33]). The locations, indications, and manipulation methods are specifically presented in Table 2. After the needle is inserted to a certain depth of the points, the acupuncturist will lift and thrust or rotate the needles to induce Deqi sensation. According to Traditional Chinese Medicine, there are 6 clinical manifestations of Deqi sensations, that are pain, numbness, distension, heaviness, dispersion, and dull pain [34,35]. After Deqi, the electroacupuncture device (CMNS6-1 [Wuxi Jia jian Medical Device Co, Ltd, China]) will be applied, connecting to points Bai Hui (GV20) and Yin Tang (GV29) with a frequency of 3 Hz, and the amplitude will vary depending on the patient’s comfort, limited between 2 and 5 mA to strengthen the needling sensation. The needle retention time is 30 minutes per session, as reported according to STRICTA guidelines.

**Figure 1. F1:**
[figure not shown]
Location of acupoints. Bai Hui (GV20), Shen Ting (GV24), Yin Tang (GV29), An Mian (EX-HN22), Shen Men (HT7), and Nei Guan (PC6).

**Table 2. T2:** Locations and manipulations of the acupuncture group and sham acupuncture group.

Acupoints	Location	Methods
GV20 (Bai Hui)	5 cun directly above the midpoint of the posterior hairline, at the midpoint of the line connecting the apexes of the two auricles.	Subcutaneous insertion 16‐26 mm.
GV24 (Shen Ting)	0.5 cun directly above the midpoint of the anterior hairline.	Subcutaneous insertion 16‐26 mm.
GV29 (Yin Tang)	On the forehead, at the midpoint between the two medial ends of the eyebrow.	Subcutaneous insertion 16‐26 mm.
EX-HN22 (An Mian)	At the middle of sternocleidomastoid tendon.	Perpendicular insertion 33‐49 mm.
HT7 (Shen Men)	At the ulnar end of the transverse crease of the wrist, in the depression on the radial side of the tendon of musculus flexor carpi ulnaris.	Perpendicular insertion 10‐16 mm.
PC6 (Nei Guan)	On the palmar side of the forearm, 2 cun above the wrist crease, between the palmar longus tendon and the radial wrist flexor tendon.	Perpendicular or oblique insertion 16‐33 mm.

### Sham Electroacupuncture Treatment (Sham Electroacupuncture Group)

Patients in the sham electroacupuncture group will receive the sham electroacupuncture intervention treatment at the same acupoints as the treatment group. We will use the placebo needle named Streitberger placebo needle from Germany in this study [36]. It is blunt without a sharp tip and cannot penetrate the skin. This kind of needle can move inside the handle and appear to be shortened after puncturing without penetrating the skin. Therefore, it is difficult for patients to distinguish between sham acupuncture and real acupuncture. The electroacupuncture device will be connected to points Bai Hui (GV20) and Yin Tang (GV29) without any electrical current.

### Assessments and Outcomes Measurement

#### Primary Outcome

The PSQI will be the primary outcome of this trial. The cross-cultural adaptation of PSQI into simplified Chinese was successful, with good reliability and validity for comprehensively evaluating the sleep quality of patients with insomnia [31]. Furthermore, PSQI is widely used to assess the effect of cancer treatment on sleep quality in patients with cancer. PSQI comprises 19 self-assessment items and is composed of 7 subscales, including sleep quality, falling asleep time, sleep duration, sleep efficiency, sleep disorders, hypnotic drug use, and daytime dysfunction. Each component is scored on a scale of 0‐3, and the total scores of PSQI range from 0 to 21. The higher the patients’ score, the worse their sleep quality and the more severe the sleep disorders, and vice versa. The primary outcome is defined as the change in PSQI total score from baseline (wk 0) to posttreatment (wk 4).

#### Secondary Outcome

##### Records of Actigraphy

Actigraphy is a portable device worn on the wrist, capable of recording and analyzing physical activity patterns. As an objective measurement method, it is commonly used to evaluate sleep-wake patterns in sleep medicine. The American Academy of Sleep Medicine has demonstrated that actigraphy is an effective tool for assessing sleep disorders and circadian sleep-wake disorders [37].

As a useful tool of sleep assessment, actigraphy is convenient, relatively low-cost, and easy to record patients’ activity for several weeks. By wearing it on the patient’s wrist, it can continuously record nighttime and daytime activity data, which can be used to analyze sleep and wakefulness patterns. Actigraphy is designed to estimate sleep latency (SOL), TST, sleep efficiency, wake after sleep onset (WASO), and the number of sleep awakenings of participants (Figure 2).

**Figure 2. F2:**
[figure not shown]
The actigraphy.

##### Insomnia Severity Index

Insomnia Severity Index (ISI) is a self-assessment scale specifically designed to evaluate the severity of insomnia. It shows good reliability, validity, and responsiveness, making it suitable for assessing sleep-related quality of life in China [38]. It has been widely used in clinical trials and research to measure the sleep quality of life of patients with cancer [39,40]. It consists of 7 items, including satisfaction of patients with insomnia with sleep quality, difficulty falling asleep, difficulty maintaining sleep, early awakening, the impact of sleep problems on daytime function, the level of concern or worry about insomnia issues, and the degree of distress caused by insomnia issues. With a total score range of 0‐28, the higher the score, the more severe the insomnia.

##### Spine Oncology Study Group Outcomes Questionnaire 2.0

The Spine Oncology Study Group Outcomes Questionnaire was developed by the Spine Oncology Study Group. In 2018, Versteeg et al [41] further validated the first version of this questionnaire and introduced the revised version, Spine Oncology Study Group Outcomes Questionnaire 2.0 (SOSGOQ 2.0). The revised version (SOSGOQ 2.0) has been extensively used in the literature to determine the effects of SM and its treatment [1,41,42]. Our term successfully verified the cross-cultural adaptation of SOSGOQ 2.0 into simplified Chinese, which demonstrated excellent acceptability, score distribution, internal consistency, test-retest reliability, and validity [4]. Therefore, the simplified Chinese version of the SOSGOQ 2.0 is considered a satisfactory tool for evaluating the health-related quality of life of Chinese patients with SM. The simplified Chinese version of the SOSGOQ 2.0 is composed of 6 health-related quality of life domains with 27 questions and 5 answer options, including physical function (6 items), neurological function (4 items), pain (5 items), mental health (2 items), social function (3 items), and posttherapy (7 items). Posttherapy questions will only be completed if the patient indicates having undergone post treatments for SM. Each question is answered via a 5-point Likert scale from 0 to 4. The overall score is calculated by summing the points of all items and excluding the posttherapy questions, with a maximum score of 80 and a minimum of 0. The higher the score, the worse the quality of life.

##### Patient Health Questionnaire-9

The Patient Health Questionnaire-9 (PHQ-9) is an effective tool for assessing the severity of depressive symptoms. The Chinese version of the depression scale, applicable to different populations, has high reliability and validity and can be used as a screening tool for evaluating the depression status of research participants [43]. PHQ-9 includes 9 items. The total scores range from 0 to 27—scores 0‐4 indicate no depressive symptoms, 5‐9 may indicate mild depressive symptoms, 10‐14 may indicate moderate depressive symptoms, 15‐19 may indicate moderate to severe depressive symptoms, and 20‐27 may indicate severe depressive symptoms.

### AEs

AEs related to electroacupuncture during this trial will be recorded in detail. A study provided information on AEs related to treatment, finding that AEs are all mild, including skin allergic reactions, hematomas, local pain, nausea, dizziness, and headache [44]. These AE data will be assessed in terms of severity and causality, and the incidence will also be determined. A 3-point grading system will be applied—grade 1 (mild), grade 2 (moderate), grade 3 (severe or medically significant). They will be recorded in the AEs form for further investigation by researchers who will analyze the causes of these events. The causality categories used will be certain, probable or likely, possible, unlikely, conditional or unclassified, and unassessable or unclassifiable. Serious AEs should be reported to the principal investigator (YC and MY) and Ethics Committee within 24 hours of occurrence.

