## Results

This study is a prospective RCT that has completed the study design and obtained ethical approval. This study was funded in June 2023. It was supported by the Project of Shanghai Key Discipline Construction Project of Traditional Chinese Medicine (Clinical Category): Digital Intelligence Acupuncture (shzyyzdxk-2024108); the Project of Shanghai Municipal Health Commission (20204Y0165, 20224Y0165); the National Natural Science Foundation of China (82205145); Shanghai “Rising Stars of Medical Talents”-Youth Development Program-Youth Medical Talents-Specialist Program (SHWSRS 2023‐062); the Youth Talent Lifting Project of the Chinese Society of Traditional Chinese Medicine (2023-QNRC2-A03); and the “Visit Famous Schools and Worship Famous Teachers” Project of Shanghai University of Traditional Chinese Medicine (079). The funders had no role in the design of the study, data collection, analysis, interpretation of data, or writing of the manuscript.

Participant recruitment is projected to start in mid-2026 and end in December 2027, with a planned recruitment of 196 participants from 5 clinical institutions. As of the submission of this manuscript, the research team has completed the training of researchers, the preparation of study materials (such as informed consent forms, CRFs, and scales), and the debugging of equipment (electroacupuncture devices and actigraphy devices). The baseline characteristics of participants will be collected after recruitment starts, including age, sex, tumor type, surgical method, time since surgery, PSQI score, ISI score, etc

Data collection will be completed in October 2027, including baseline assessment (wk 0), treatment process records (weekly), posttreatment assessment (wk 4), and follow-up assessment (wk 12). Actigraphy monitoring will be conducted at week 0, week 1, week 2, week 3, and week 4 to collect objective sleep data. AEs will be recorded in real-time during the study period.

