Data analysis is expected to be completed in December 2027. The primary analysis will focus on the difference in PSQI score changes between the electroacupuncture group and the sham electroacupuncture group based on the ITT population. Secondary analyses will include comparisons of actigraphy indicators, ISI score, SOSGOQ 2.0 score, and PHQ-9 score between the 2 groups at posttreatment and follow-up. Subgroup and sensitivity analyses will be performed to verify the robustness of the results. Safety analysis will evaluate the incidence and severity of AEs in both groups. The study results are anticipated to be published in the first half of 2028.

The trial flow chart is illustrated in Figure 3.

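### The adverse-event section opens with a rule that, read literally, records only events related to electroacupuncture; this conflicts with the rest of the protocol and should be reworded before recruitment.

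*Protocol article*

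**What the plan says.** The only section of the protocol article devoted to adverse events (AEs) begins: "AEs related to electroacupuncture during this trial will be recorded in detail". It continues: "These AE data will be assessed in terms of severity and causality, and the incidence will also be determined". The six causality grades are "certain, probable or likely, possible, unlikely, conditional or unclassified, and unassessable or unclassifiable". The events go onto an AE form, and researchers then look into their causes. Serious events go to the principal investigator "and Ethics Committee within 24 hours of occurrence", with no condition on relatedness.

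Other places that bear on AE collection:

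- **Table 1** (Study Design and Setting) has two rows. One, on the safety of electroacupuncture, is ticked for weeks 1 to 4. The other, for adverse events in general, is ticked for weeks 1 to 4, 8 and 16.
- **Analysis Populations** defines the safety population as everyone with at least one session and bases the AE analysis on it.
- **Results** says "AEs will be recorded in real-time during the study period" and "Safety analysis will evaluate the incidence and severity of AEs in both groups".
- **Introduction**, third hypothesis: electroacupuncture is safe, with few AEs.
- **Sham Electroacupuncture Treatment**: a blunt, non-penetrating needle, and a device connected without current.
- **Blinding**: "Except for the acupuncturists, other personnel, including all participants, outcome assessors, data analysts, and statisticians, will be blinded". The Intervention section adds the investigators and study staff to those who are blinded.

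**The concern.** An AE collection rule should take in events first and judge cause afterwards. The opening sentence of the AEs section, taken alone, reverses that order: an event must be related to electroacupuncture before it is recorded.

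Three things make this more than a matter of style.

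- Patients in the sham arm do not receive electroacupuncture, so a site has no defined way to apply the condition to them, yet their events are the comparator.
- The events that the section expects include local pain, nausea, dizziness and headache. The Introduction says that these patients may have persistent pain and neurological irritation after surgery. Relatedness is then a judgement call.
- An event that was never recorded cannot be recovered at analysis, and the data and safety monitoring board would see only what was recorded.

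At stake are the safety hypothesis, which rests on incidence, and the description of AEs by group.

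**Working it through.** No figure in the documents bears on this point, so the check is mainly a comparison of the passages.

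**Step 1. Does the opening sentence agree with the rest?**

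| Place | What it implies about recording |
|---|---|
| AEs, first sentence | Events related to electroacupuncture |
| AEs, causality scale | Includes events unlikely to be related or not assessable |
| AEs, use of the AE form | Events entered, then causes analysed |
| AEs, serious events | No relatedness condition |
| Table 1 | General AE row to week 16, separate from the electroacupuncture safety row |
| Analysis Populations | All treated patients, both arms, no relatedness filter |
| Results | Recording in real time, evaluation in both groups, no filter |

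The first sentence stands against the other six. The clash with the causality scale is the sharpest: an event admitted because it is related cannot sensibly be graded unlikely. A site that follows the first sentence and a site that follows the Results section could collect different events.

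**Step 2. What would a literal reading do?** This is an illustration only; every rate and share is assumed. Let p be the true AE rate, the same in both arms, and s the share of events judged related. The recorded rate is p × s. With 98 patients per arm, all treated, the approximate chance of a falsely significant difference at two-sided 0.05 is

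Φ[(d − 1.96 × se0) / se1],

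where d is the recorded difference, se0 its standard error with the pooled rate, and se1 its standard error with separate rates.

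| p | s active | s sham | Recorded active | Recorded sham | Chance of a false difference |
|---|---|---|---|---|---|
| 20% | 50% | 50% | 0.20 × 0.50 = 10% | 0.20 × 0.50 = 10% | 5% (nominal) |
| 20% | 50% | 25% | 10% | 0.20 × 0.25 = 5% | about 26% |
| 40% | 50% | 50% | 0.40 × 0.50 = 20% | 20% | 5% (nominal) |
| 40% | 50% | 25% | 20% | 0.40 × 0.25 = 10% | about 50% |

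For the second row:

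- se0 = √(2 × 0.075 × 0.925 / 98) = 0.0376
- se1 = √((0.10 × 0.90 + 0.05 × 0.95) / 98) = 0.0375
- (0.05 − 1.96 × 0.0376) / 0.0375 = −0.63, and Φ(−0.63) ≈ 0.26

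Two separate effects appear. Equal attribution halves the recorded incidence in these examples but creates no difference between arms. Unequal attribution also creates a difference where none exists. Swapping the shares would reverse its direction.

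**The case against.** The strongest reply is that the article, read as a whole, already describes sound practice. The opening sentence does not say that only related events are recorded. The AEs section puts the form first and the analysis of causes second. The causality grades would be pointless if relatedness were an entry filter. Table 1, the safety population and the Results section are all unrestricted. Nothing gives the opening sentence precedence over them. The full AE form and CRF instructions are not shown and cannot be presumed restrictive.

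Most of this stands, and it rules out three stronger readings that a reader might infer.

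- **That the trial limits recording and so cannot compare the arms fairly.** The other passages suggest that recording all events may well be intended.
- **That the unblinded acupuncturist decides what counts as related.** No passage says so. Cause analysis is given to researchers, and everyone except the acupuncturists is described as blinded.
- **That a bias of a particular size is to be expected.** Any such figure comes wholly from the assumed attribution shares. The article also states no formal test of AEs between arms, and its safety hypothesis concerns a low incidence and makes no comparison.

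The reply does not remove the inconsistency. The sentence is the stated rule in the one section that site staff would consult on AEs. It is a statement in the text, not a detail left to another document.

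**Conclusion.** The point holds as an internal inconsistency in a collection rule. The first sentence of the AEs section cannot be reconciled with the causality scale beneath it, Table 1, the safety population or the Results section, and it leaves sham-arm events ill-defined.

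The consequence is conditional. If sites applied the sentence literally, recorded incidence would be too low, which bears directly on the safety hypothesis. If they also attributed events differently by arm, the comparison between groups would be biased in a direction that cannot be foreseen. With equal attribution there would be no spurious difference. The size of either effect is unknown.

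This should be corrected, because a lost event cannot be restored later and the correction is small. It does not by itself invalidate the planned safety evaluation.

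**What to change.** Reword the opening of the AEs section so that all adverse events in both arms are recorded from the first session to the last follow-up, whatever the suspected cause. State that causality is assigned afterwards, on the existing six-grade scale, by study personnel who are already blinded to group. Report all-cause AEs by arm first, then treatment-related AEs.

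Check that the CRF and AE-form instructions carry the same rule. The Results section says that the CRFs are already prepared and that recruitment is still to come, so the check belongs before the first patient is enrolled.

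The cost is a sentence or two in the protocol, a check of the CRF instructions, and more unrelated events to record and grade in a cancer population.

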#### Inclusion Criteria

First, male or female participants who were aged 18 years or older. This age limit is set because adults have relatively stable physiological functions and can better cooperate with the treatment and evaluation process.

Second, patients diagnosed with SM based on cytological or histopathological features, and undergone SM surgery within 1‐2 weeks. This time interval is determined because sleep disturbance after SM surgery is most prominent within 1‐2 weeks postoperatively, and intervention during this period is more conducive to improving rehabilitation outcomes.

Third, the PSQI score was >11. Patients with chronic insomnia disorder (defined as insomnia lasting ≥3 months before surgery) are excluded. According to the validation study of the Chinese version of PSQI, a score >11 indicates moderate to severe insomnia, which is a reasonable threshold for selecting patients with clinically significant postoperative insomnia [31,32].

Fourth, have an estimated survival period of at least 6 months. This is to ensure that participants can complete the entire treatment and follow-up process, and avoid the impact of patient death on the study results. The survival period is estimated by the attending physician based on the patient’s tumor type, stage, treatment response, and other factors.

Fifth, consent to participation and completion of the full treatment process, and provide written consent.

Sixth, postoperative blood examination showed no obvious abnormality, indicating that the patient’s general condition is stable and can tolerate electroacupuncture treatment.

Finally, no history of shift work in the past 6 months. Shift work can independently affect sleep patterns and confound the study results, so such individuals are excluded.

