### Data Security and Monitoring

We will establish an independent DSMB to monitor whether the study design meets guideline standards to ensure the rigor of the trial. The committee consists of 5 members from different fields. Members of the DSMB must declare that there are no conflicts of interest to ensure the independence of their decisions. The DSMB will periodically review the accumulated data from clinical trials, assess the risks and benefits during the trial process, and ensure the safety of the patients. Based on the review of the data, the DSMB can advise the researchers to continue, modify, or suspend the trial. If serious AEs occur, they have the right to suspend or terminate the trial.

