### Analysis Populations and Missing Data Handling (SPIRIT Item 20c)

#### Analysis Populations

Intention-to-treat (ITT) population includes all randomized participants, regardless of protocol adherence, withdrawal, or missing data. This population will be used for the primary analysis to maintain the advantages of randomization and reduce selection bias.

Per-protocol population includes participants who completed the full course of treatment, had no major protocol violations, and provided complete outcome data. This population will be used for secondary analysis to evaluate the efficacy under ideal conditions.

Safety population includes all participants who received at least 1 session of treatment. AEs will be analyzed based on this population.

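### The three-level adverse-event scale has no level for life-threatening or fatal events and mixes intensity with medical significance, so the severity comparison by arm cannot separate them by grade (minor)

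*Protocol article*

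**What the plan says.** Under AEs, the protocol article states the scale outright: "grade 1 (mild), grade 2 (moderate), grade 3 (severe or medically significant"). The section opens with its scope, "AEs related to electroacupuncture during this trial will be recorded in detail", and cites a study whose events were all mild, "including skin allergic reactions, hematomas, local pain, nausea, dizziness, and headache". Events are also assessed for causality, in categories that include unlikely.

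Seriousness has its own rule in the same section: "Serious AEs should be reported to the principal investigator" and the Ethics Committee within 24 hours. Under Data Security and Monitoring, the DSMB's power is likewise tied to seriousness: "If serious AEs occur, they have the right to suspend or terminate the trial".

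On analysis, the Results section says: "Safety analysis will evaluate the incidence and severity of AEs in both groups". The Analysis Populations section defines the safety population as everyone who received at least one session and adds: "AEs will be analyzed based on this population".

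The fourth inclusion criterion requires an estimated survival of at least 6 months, partly to "avoid the impact of patient death on the study results".

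**The concern.** A mild/moderate/severe scale suits a trial in which only minor needling reactions are expected. This trial enrols patients within two weeks of surgery for spinal metastases, and its own survival criterion shows that death was considered. The announced safety comparison relies on severity, yet the scale cannot show the worst outcomes as a category of their own. If one arm had more life-threatening or fatal events and the other more severe but self-limiting ones, the grade 3 rows could look the same.

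The wording of the top level adds a second difficulty. Severity describes how intense an event is; medical significance is a criterion of seriousness. An event of moderate intensity that is medically significant meets the descriptions of both grade 2 and grade 3, and two centres could code it differently.

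**Working it through.** No arithmetic applies. The claim concerns the categories of a scale and depends on no rate, effect size or sample size. The check is to place events on the stated scale and then look for any other text that supplies what is missing.

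**Step 1. Place events on the scale (AEs section).**

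- Severe headache that resolves: grade 3, by intensity.
- Moderate event that is medically significant: grade 2 by intensity, grade 3 by significance.
- Life-threatening event: grade 3, or ungraded.
- Death: grade 3, or ungraded.

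**Step 2. Look for a higher level or another scale.** The places that deal with safety are the third hypothesis in the Introduction, Table 1, AEs, Data Security and Monitoring, Analysis Populations, Results and Strengths of the Study. None adds a level, names a different scale or gives a rule for life-threatening or fatal events.

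**Step 3. Look for a separate tabulation.** The Results section promises "Safety analysis will evaluate the incidence and severity of AEs in both groups", and Analysis Populations names the set of participants. Neither says that serious or fatal AEs will be shown separately by arm.

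**Step 4. Ask whether the grade controls oversight.** It does not. The 24-hour report and the DSMB's power to suspend or terminate both depend on an event being serious, and neither rule refers to a grade. The article does not define seriousness or link it to the scale.

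**Step 5. Ask which events reach the scale.** The AEs section opens with events related to electroacupuncture, but its causality categories include unlikely, so some events not attributed to needling may be entered too. A death from the underlying cancer could therefore be coded grade 3 or fall outside the scale. In neither case does the severity table identify it by grade.

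**Result.** The severity comparison by arm cannot separate life-threatening and fatal events, by grade, from severe non-serious ones. That is the whole of the defect.

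**The case against.** The strongest reply is that severity and seriousness already run on separate tracks, and that a three-level intensity scale is adequate when seriousness is recorded as its own attribute. The separation of the reporting rules stands, and it is why the point is minor. It does not fully answer the concern, because the top grade itself brings medical significance into the intensity scale.

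A second reply is that a journal article condenses. The definition of a serious event, the fields of the AE form and the table layouts may be set out in the full protocol, the case report form or the analysis plan, none of which is shown. That also stands, and the absence of these items is not held against the article. What remains is the scale, which the article does state and which fits this population poorly.

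A reader might infer three stronger things that the document does not support:

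- **That the DSMB would see only the collapsed grades.** The article describes no DSMB tables. It says that accumulated data are reviewed periodically.
- **That deaths could not be told apart from other grade 3 events at all.** Events are recorded in detail on an AE form and investigated, and incidence is reported as well as severity. A death stays identifiable as an event; only the summary by grade merges it.
- **That many deaths would be hidden.** The article gives no mortality figure. The survival criterion is there to limit deaths during the study and does not forecast them. All-cause deaths would also be a poor measure of the problem, given the opening scope of the AEs section.

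That sites will treat grade 3 and serious as the same thing is possible, but no text links the two.

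**Conclusion.** The point holds as a minor weakness in safety reporting. The stated scale ends at a level that mixes intensity with medical significance, and it provides no category for life-threatening or fatal events. The announced severity comparison therefore cannot separate them by grade. Oversight of such events is intact through the serious-AE report and the DSMB. The primary efficacy analysis and the sample size are unaffected.

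No numerical size is attached, because the document gives no rate from which one could be derived, and the argument does not need one. The conclusion assumes that no document outside the article supplies a finer scale or a separate table of serious and fatal AEs. If one does, all that remains is to bring the article's wording into line with it.

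**What to change.** In the AEs section, replace the three-level scale with five levels: mild, moderate, severe, life-threatening, fatal. Take medical significance out of the grade, and record seriousness as a separate yes/no item on the AE form. In the safety analysis, state that grades 3, 4 and 5, and serious AEs, will each be tabulated separately by arm in the safety population.

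The cost is a few sentences, a revised AE form and brief site training. The Results section says that the case report forms are already prepared, so the AE form would have to be reissued. It also describes recruitment as still to start, so making the change now should require no regrading of collected events. A change made during the trial would.
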